##### Relatedness assessment

Definite: Clear temporal relationship with study procedure; no alternative explanationProbable: Temporal relationship consistent with study procedure; alternative explanation less likelyPossible: Temporal relationship uncertain; alternative explanations possibleUnrelated: Clear alternative explanation; temporal relationship inconsistent

#### Standardized language

Harms will be documented using descriptive terminology aligned with common cardiovascular and respiratory symptom classifications. VR-specific symptoms will be documented using standard cybersickness terminology (nausea, dizziness, disorientation, headache, eye strain).

#### Reporting approach for adverse events

All serious adverse events will be reported, defined as events requiring hospitalization, causing persistent incapacity, resulting in permanent disability or potentially life-threatening. All VR-related adverse events will be reported, defined as cybersickness symptoms (nausea, dizziness, disorientation, headache, eye strain) occurring during or immediately after study procedures. All exercise-stopping events will be reported, defined as any adverse event leading to early session termination before planned protocol completion. Adverse events occurring in ≥ 5% of participants in either group will be reported. Any adverse event causing permanent harm will be reported. Non-serious adverse events not meeting above criteria may be summarized descriptively but will not be listed individually in results.

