**Methods:**

We will conduct a randomized, controlled, parallel-group trial with 1:1 allocation. Adult inpatients with a diagnosis of HF will be screened for eligibility and randomly assigned to two groups: control (cycle-ergometer aerobic exercise) and intervention (the same exercise combined with an Meta Quest 2 VR device). Each participant will complete a single session of up to 20 min, consisting of five blocks of 3 min of continuous pedaling interspersed with one-minute passive rests, with early termination in case of intolerance. The primary outcome is effective exercise time (minutes) until interruption due to physical limitation or symptoms. Secondary outcomes include rating of perceived exertion, hemodynamic parameters, exercise enjoyment (PACES) and usability of the technology (SUS, intervention group only).

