## Methods: participants, interventions and outcomes

### Trial setting {13}

The study will be conducted on inpatient units in the Cardiology and Cardiac Surgery departments of Hospital São Paulo, São Paulo, Brazil. This referral hospital provides infrastructure for monitoring patients during interventions, including a qualified multidisciplinary team and all resources necessary to ensure participant safety and well-being.

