#### Harms classification and standardization

##### Severity classification

Mild: Uncomfortable but does not interfere with daily function; resolves spontaneously or with minimal interventionModerate: Interferes with daily function or requires medical intervention; may persistSevere: Incapacitating; requires hospitalization or prevents exercise continuation; potentially life-threatening

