##### Serious adverse event reporting

Any serious adverse event (as defined in Reporting Approach section) occurring during or within 24 h post-exercise will be reported to the principal investigator immediately (within 2 h of identification). Serious adverse events will be reported to the Research Ethics Committee of UNIFESP within 48 h. All events will be assessed for temporal and causal relationship to study procedures using standardized relatedness categories (definite, probable, possible, unrelated). If a pattern of concerning adverse events emerges (≥ 2 serious events potentially related to study procedures), the principal investigator will assess whether Data Safety Monitoring Board review or study pause is warranted.

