**POST-EXERCISE ASSESSMENTS**				
Total exercise time (minutes) (g)				X
Recovery vital signs				X
SUS—VR group only (i)				X
PACES (h)				X
Adverse events assessment (j,k)				X

a) Single-session design: Only ONE exercise session per participant during hospitalization.

b) Timepoints: Enrollment → Randomization → Intervention → Post-Exercise/Close-Out. No follow-up.

c) Both groups identical protocol except: VR group receives immersive VR headset; control group receives standard cycle ergometer.

d) Hospital Anxiety and Depression Scale (HADS): 14-item self-report questionnaire assessing anxiety (7 items, score 0–21) and depression (7 items, score 0–21) during acute hospitalization [24, 25]

e) Continuous vital signs monitoring: Blood pressure (BP, mmHg, systolic/diastolic), heart rate (HR, bpm), peripheral oxygen saturation (SpO₂, %) and respiratory rate (RR, breaths/min) recorded every minute throughout exercise and recovery period via automated monitors and continuous 12-lead ECG.

f) Session termination criteria: Immediate termination triggered if Rating of Perceived Exertion (RPE) ≥ 5 (‘hard’ intensity) OR if any safety threshold exceeded: BP > 200 mmHg or < 80 mmHg (systolic), HR > 130 or < 40 bpm,SpO₂ < 85% or ST-segment changes on ECG.

g) Total exercise time: Cumulative pedaling time (minutes) from initiation to termination.

h) Physical Activity Enjoyment Scale (PACES): 18-item questionnaire (score 18–80); higher = greater enjoyment [18, 19]

i) System Usability Scale (SUS10-item questionnaire (score 0–100); ≥ 68 indicates above-average usability; ≥ 70 considered acceptable for clinical implementation [20, 21]

j) Adverse events: Serious (requiring intervention) vs. non-serious. Documented immediately post-exercise.

k) Real-time data collection: All vital signs, RPE, observations recorded by physiotherapist on paper CRF during exercise; transferred to REDCap same day.

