#### Composition of the data monitoring committee, its role and reporting structure {28a}

No Data Monitoring Committee (DMC) is planned given the low-risk intervention and continuous oversight by experienced professionals. Participant safety will be regularly monitored by the main research team. Any serious adverse event will prompt appropriate action in accordance with institutional safety/ethics guidance. Safety oversight will be supervised by the institutional Research Ethics Committee.

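### The serious-adverse-event definition relies in part on hospitalization in an all-inpatient trial, conflicts with the timeline's definition, and the review rule names a board that is not planned

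*Protocol article*

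**What the plan says.** The population is hospitalized: "Adult inpatients with a diagnosis of HF will be screened for eligibility", and the Trial setting section says "The study will be conducted on inpatient units".

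Seriousness is described in two places:

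- Reporting approach for adverse events: serious events are "defined as events requiring hospitalization, causing persistent incapacity, resulting in permanent disability or potentially life-threatening".
- Participant timeline, footnote j: "Adverse events: Serious (requiring intervention) vs. non-serious. Documented immediately post-exercise".

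The Severity classification is a separate scale. Its top grade reads "Incapacitating; requires hospitalization or prevents exercise continuation; potentially life-threatening". Its middle grade covers events that need medical intervention, and its lowest grade allows minimal intervention.

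Serious adverse event reporting adopts the Reporting approach definition by explicit cross-reference. It covers events during exercise or in the following 24 h, and requires notice to the principal investigator within 2 h and to the Research Ethics Committee within 48 h. At two or more potentially related serious events, "the principal investigator will assess whether Data Safety Monitoring Board review or study pause is warranted".

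The section on the data monitoring committee says "No Data Monitoring Committee (DMC) is planned given the low-risk intervention", and the section on the coordinating centre likewise plans no monitoring or adjudication committee. Data analysis approach for harms sends suspected safety signals to the research team and the Ethics Committee.

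**The concern.** A seriousness criterion has to sort events. One that asks about hospitalization sorts them in outpatients, where admission is a change of state. Here nobody can be newly admitted. The usual inpatient counterpart, prolongation of the existing stay, is absent, and so is death. What is at stake is whether an event that lengthens an admission enters the expedited reports and the two-event count.

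The timeline footnote adds a second problem. It sits in the assessment schedule that staff follow when they record events, and its test is broader than the one that governs reporting. The seriousness entered on the form and the seriousness used for reporting can then disagree. Third, a review step that names a body the trial does not plan leaves unclear who would carry out that review.

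**Working it through.** The article states no figure on this point, so there is none to reproduce. The check is to run example events through the three classifications.

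| Event | Reporting approach definition | Footnote j | Severity classification |
|---|---|---|---|
| Treated event that lengthens the stay, neither disabling nor potentially life-threatening | Unclear; not serious on the literal criteria | Serious | Moderate, or severe if the session could not continue |
| Stay lengthened for observation only | Unclear; not serious on the literal criteria | Not serious | Not settled by the wording |
| Brief nausea, treated and resolved | Not serious | Serious | Mild if treatment is minimal, otherwise moderate; severe if it ended the session |
| Death | Not named; reached through the life-threatening criterion | Not named | Not named; reached through the life-threatening wording |

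The first and third rows show the conflict between the two seriousness tests. The first two show the gap over prolonged stay. The severity scale does not close that gap, because its top grade uses the same hospitalization wording.

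**Would such an event surface anyway in the results?** Reporting approach also lists cybersickness events, session-stopping events, events causing permanent harm, and events in at least 5% of either group. With 30 per group (Sample size), one affected participant is 1/30 = 3.3%, below 5%; two are 2/30 = 6.7%. A single delayed, stay-prolonging event that did not stop the session, was not cybersickness and caused no permanent harm therefore meets none of the listing criteria unless it is classed as serious.

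**How sensitive is the two-event count to what is counted?** The document gives no rate, so the rates here are assumptions. Take N = 60, independent participants with probability p of a qualifying, potentially related event:

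P(at least 2 participants) = 1 − (1 − p)^60 − 60p(1 − p)^59

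| Assumed p | P(at least 2 of 60) |
|---|---|
| 0.5% | 0.04 |
| 1% | 0.12 |
| 2% | 0.34 |
| 5% | 0.81 |

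If, for illustration, counting stay-prolonging events moved p from 1% to 2%, the chance of reaching the count would move from 0.12 to 0.34. This shows direction only.

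**Capture window.** Footnote b says there is no follow-up and footnote j places documentation immediately after exercise. Post-session assessment asks participants to telephone about delayed symptoms within 24 h, and the serious-event rule runs to 24 h. These can be read together, with the footnotes describing scheduled assessments, but the footnotes do not say so.

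**Review body.** Serious adverse event reporting names a board, two oversight sections plan none, and the harms analysis section uses the research team and Ethics Committee.

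**The case against.** The strongest reply is that little depends on these wordings. Much of it stands.

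- A reader might infer that the whole definition hinges on hospitalization. It does not: that is one of four alternative criteria, and the other three work in inpatients. A fatal event would in practice be caught as life-threatening.
- A reader might infer that footnote j feeds the two-event rule, and compare a narrow rate of 1% with a broad rate of 5% or more, so that the chance of reaching the count jumps from 0.12 to 0.81 or higher. The documents do not support this, because the rule explicitly takes the Reporting approach definition.
- A reader might infer that this is the only route to a pause, that a board takes the decision, or that one reclassified event settles whether the trial is reviewed. None of these holds. The principal investigator decides, and board review is one of two options. The harms analysis section lists a pause among possible actions and needs no count of two. The Interim analyses section allows interruption on clinical or ethical grounds. Every recognized serious event goes to the Ethics Committee within 48 h whatever the count.
- A reader might expect damage to a between-arm test of serious events. The article plans chi-square comparisons of adverse event rates and specifies no separate test for serious ones.
- Nothing in the document shows that a longer admission is the most likely serious outcome.

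It can also be argued that an event needing further hospital care falls under the hospitalization criterion on a sensible reading. That reading is possible, but the text does not state it, and staff should not have to supply it. The 48 h safeguard protects only events first recognized as serious, which is where the gap lies.

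**Conclusion.** The point holds as a defect in safety definitions and cross-references. As written, a stay-prolonging event that is neither disabling nor potentially life-threatening may be left out of expedited reporting and of the two-event count. Seriousness recorded under the timeline can differ from seriousness under the reporting sections. The board named in the review rule is not one the trial plans.

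The number of events affected cannot be given. The probabilities shown rest on assumed rates, independence, and every event being judged potentially related. The conclusion itself rests only on the text and on the literal reading of the hospitalization criterion; the conflict between definitions and the unplanned board do not depend on that reading. The primary outcome and its analysis are untouched. The point should be fixed because the gap concerns participant safety and the remedy is cheap.

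**What to change.** - Use one seriousness definition in Reporting approach, Serious adverse event reporting and footnote j that works for inpatients: death, life-threatening, prolongation of the existing hospitalization, or persistent or significant disability or incapacity.
- Remove need for intervention as the test in footnote j. Keep it as the separate field that Definition and assessment of harms already lists.
- State in footnotes b and j that capture of serious events runs to 24 h, as Post-session assessment and Serious adverse event reporting already have it.
- Reconcile the review body in Serious adverse event reporting with Data analysis approach for harms and the two oversight sections, so that all name the same arrangement.

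The cost is protocol and CRF wording, and possibly a few more reported serious events. Trial status gives a recruitment start of 10 November 2025, so events already recorded would need a check against the single definition. If the change is treated as substantial, it follows the article's own amendment procedure.

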##### Post-session assessment

Vital signs (BP, HR, RR, SpO₂) will be assessed at 1-min post-exercise and monitored continuously until participant hemodynamic stability is confirmed (typically 5 min). Participants will be instructed to report any delayed adverse symptoms (occurring > 1 h after exercise completion) within 24 h via telephone contact with research team. Contact information will be provided to all participants before exercise begins.

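### The definition of VR-related adverse events is narrower than the protocol's own list of VR-specific harms and its delayed-symptom collection, so the count under that label would be incomplete whenever such events occur

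*Protocol article*

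**What the plan says.** All places are in the protocol article, mostly under Harms {17}.

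- **Definition.** Reporting approach for adverse events: "All VR-related adverse events will be reported, defined as cybersickness symptoms (nausea, dizziness, disorientation, headache, eye strain) occurring during or immediately after study procedures".
- **List of harms.** VR-specific harms (intervention group only) has two parts. The cybersickness part pairs nausea with vomiting, dizziness with vertigo, and headache with eye strain, and adds disorientation. The device-related part names skin irritation caused by the headset and malfunction that makes the equipment unsafe to use.
- **Delayed symptoms.** Post-session assessment: "Participants will be instructed to report any delayed adverse symptoms (occurring > 1 h after exercise completion) within 24 h". The route is a telephone call to the team.
- **Schedule.** The Participant timeline {18} note on adverse events says "Documented immediately post-exercise", and another note rules out follow-up.
- **Other routes to reporting.** A frequency rule applies whatever the type of event: "Adverse events occurring in ≥ 5% of participants in either group will be reported". Serious events, events that end the session early and events causing permanent harm are reported however rare they are.
- **Everything else.** "Non-serious adverse events not meeting above criteria may be summarized descriptively but will not be listed individually in results".
- **Analysis.** Data analysis approach for harms compares event counts and affected participants between groups across all adverse events. There, VR-specific harms are glossed as cybersickness symptoms. Standardized language gives the same five terms as the definition.

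**The concern.** The promise is complete reporting of VR-related events, but the definition attached to it does not cover what the protocol elsewhere calls VR-specific, or what it asks participants to report later. It works by symptom name and timing and makes no use of the relatedness scale. A skin reaction judged definitely due to the headset would not be VR-related, while a listed symptom in the window counts whatever its judged cause.

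VR-related symptoms are part of a secondary safety objective (Objectives {10}). A results table under this label would look complete and could lack device-related and delayed events. With 30 patients wearing the headset, part of the tolerability profile may consist of isolated cases, so the wording of the label has some influence on what readers see.

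**Working it through.** The plan gives no figure to reproduce here. The check compares the texts and then asks what the other reporting routes would catch.

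**Step 1: list against definition.**

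| VR-specific harm as listed | Under the definition |
|---|---|
| Nausea or vomiting | Nausea named; vomiting can be coded with it |
| Dizziness or vertigo | Dizziness named; vertigo can be coded with it |
| Disorientation | Named |
| Headache or eye strain | Both named |
| Headset skin irritation | No counterpart |
| Equipment malfunction | No counterpart |

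Four of the six lines have a counterpart. The two device-related lines have none.

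**Step 2: time window against collection.** The definition ends immediately after study procedures. Solicited delayed symptoms begin more than 1 h after exercise. The two do not overlap, so a headache three hours later is asked for but cannot carry the label. The schedule note, which places documentation directly after exercise, does not reflect the later route either.

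**Step 3: the 5% route.** Inputs: 30 per group and 10% dropout (Sample size {19}).

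- n = 30: 0.05 × 30 = 1.5, so 2 participants are needed. 1/30 = 3.3% misses; 2/30 = 6.7% qualifies.
- n = 30 × 0.9 = 27: 0.05 × 27 = 1.35, so again 2. 1/27 = 3.7%; 2/27 = 7.4%.

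An event outside the definition that is non-serious, did not stop the session and left no permanent harm is therefore not individually listed if it affects one participant.

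**Step 4: how often that could happen.** The documents give no harm rates, so the true risk p of one omitted harm type is assumed over a range. With n = 30:

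- P(0) = (1 − p)^30
- P(1) = 30 × p × (1 − p)^29
- P(2 or more) = 1 − P(0) − P(1)

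| Assumed p | P(0) | P(exactly 1) | P(2 or more) | P(exactly 1, given at least 1) |
|---|---|---|---|---|
| 1% | 0.740 | 0.224 | 0.036 | 0.861 |
| 2% | 0.545 | 0.334 | 0.121 | 0.735 |
| 3% | 0.401 | 0.372 | 0.227 | 0.621 |
| 5% | 0.215 | 0.339 | 0.446 | 0.432 |
| 10% | 0.042 | 0.141 | 0.816 | 0.148 |

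For an assumed risk of 1% to 5%, there is a 22% to 37% chance that the harm appears in exactly one VR participant and so misses the 5% route.

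This applies most directly to mild skin irritation with the session completed. It does not carry over simply to delayed symptoms: the 5% rule has no time window, so one delayed and one immediate headache in two participants of the same group would meet it.

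**The case against.** The strongest reply is that little is lost. All harms are to be assessed systematically, with type, timing, severity and relatedness recorded. The between-group comparison covers all adverse events and is not limited to the five symptoms. Serious events are followed to 24 h. Every single case of the five named symptoms in the immediate window is reported, with no 5% threshold, so the main VR harms are well served. A tight window is also a defensible choice for acute cybersickness. All of this stands, and it confines the point to a label and to isolated mild events.

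A reader might go further and infer that four of nine VR-specific harms are left out and that VR harm is undercounted. The documents do not support that. Nine arises only by splitting paired entries, and vomiting and vertigo can be recorded under nausea and dizziness in the standard terminology. A malfunction that makes use unsafe would probably end the session and be reported as exercise-stopping if it is recorded as an adverse event. Omitted events remain in the overall comparison, so only the count carrying the VR-related label is short, and only if such events occur.

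It can also be said that listing rules belong in a fuller document. That would answer a missing detail. Here the article itself fixes the definition and sets it against its own list and its own collection, and the sections on terminology and analysis repeat the narrow version.

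**Conclusion.** The point holds as a minor inconsistency in the definition. The VR-related count would omit headset skin irritation and symptoms arising more than 1 h after exercise, whatever their frequency. Individual listing would be lost only for an event that is mild, non-serious, non-stopping and without permanent harm, and at most for one participant per omitted harm type in the VR group, since two of 30 (or of 27) already reach 5%.

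The mismatch and the two-participant threshold follow from the text and the planned group size. The probabilities of a single case rest on assumed risks. Neither the primary result nor the overall harms comparison is affected.

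**What to change.** In Reporting approach for adverse events, define a VR-related adverse event as any harm in the VR-specific list, with vomiting, vertigo and headset skin irritation named, that arises from headset fitting to 24 h after exercise and is judged at least possibly related on the Relatedness assessment scale. The relatedness condition is needed: a 24 h window alone would attribute any next-day headache or nausea in an inpatient to the headset.

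Show immediate and delayed events separately, so that the acute cybersickness count stays visible. Report device malfunctions on their own line. Align Standardized language, Data analysis approach for harms and the Participant timeline note on documentation with the new definition.

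The cost is a wording change. The telephone route already exists, and relatedness is already to be recorded for every adverse event. The stated VR-related count may be slightly higher, and delayed symptoms will need a relatedness judgement that is less certain than for events during the session.
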